### Decision criteria

Latent (so called "subclinical") thyrotoxicosis is defined as suppressed thyrotropin levels with free T4 levels being in their reference intervals and additional clinical evidence for tissue hyperthyroidism (suggestive history or Burch-Wartofsky point scale of more than 45 points [23]). Decision criteria to be evaluated are reproduced in Table 2.

### Calculations

Thyrotroph T4 Sensitivity Index (TTSI) is calculated as

(1)$$TTSI=\frac{100[TSH][FT_{4}]}{l_{u}}$$

with *l*_*u *_being the upper limit of the reference interval for free T4 [24]. Theoretical secretion capacity of the thyroid gland (G_T_^) is computed with

(2)$${\hat{G}}_{T}=\frac{\beta_{T}(D_{T}+[TSH])(1+K_{41}[TBG]+K_{42}[TBPA])[FT_{4}]}{\alpha_{T}[TSH]},$$

where parameters are taken from Table 4[21].

**Table 4 T4:** Parameters for structure parameter inference [21]

**Symbol**	**Explanation**	**Value**
α_T_	Dilution factor for T4 (reciprocal of apparent volume of distribution)	0,1 l^-1^
β_T_	Clearance exponent for T4	1,1 * 10^-6 ^sec^-1^
D_T_	EC_50 _for TSH	2,75 mU/l
K_41_	Dissociation constant T4-TBG	2 * 10^10 ^l/mol
		
K_42_	Dissociation constant T4-TBPA	2 * 10^8 ^l/mol
		
α _31_	Dilution factor for T3	0,026 l^-1^
β _31_	Clearance exponent for T3	8 * 10^-6 ^sec^-1^
K_M1_	Dissociation constant of type-1-deiodinase	5 * 10^-7 ^mol/l
		
K_30_	Dissociation constant T3-TBG	2 * 10^9 ^l/mol

Sum activity of peripheral 5'-deiodinase (G_D_^) is defined with

(3)$${\hat{G}}_{D}=\frac{\beta_{31}(K_{M1}+[FT_{4}])(1+K_{30}[TBG])[FT_{3}]}{\alpha_{31}[FT_{4}]},$$

parameters are again from Table 4[21].

Apparent dissociation constant of T3 binding to TBG is obtained with

(4)$${\hat{K}}_{30}=\frac{\left[T_{3}]-[FT_{3}\right]}{\left[TBG][FT_{3}\right]}$$

from levels of iodothyronines and TBG.

Relative binding ratio is calculated with

(5)$$R_{B}=\frac{\frac{\left[T_{3}\right]}{l_{l,TT3}}}{\frac{\left[FT_{3}\right]}{l_{l,FT3}}}$$

where *l*_*l*, *TT*3 _denotes the lower limit of the reference interval for TT3 and *l*_*l*, *FT*3 _is the lower limit of the reference interval for FT3.

### Follow-up and Evaluation Points

Patients are subjected to at least one evaluation point. Critically ill persons that are newly admitted to an ICU are screened in the first EP (1.0) for fulfilment of the inclusion and exclusion criteria from Table 3 and entered in the database (see below). The second EP (1.1) is performed after 24 hours; only those eligible patients that are still under intensive care will be included in the study and subsequently prospectively observed. On the occasion of this and the subsequent EPs (after 72 hours for EP 1.2 and weekly in the further course of the study), severity scores like SAPS II and APACHE II as well as physiological parameters and data regarding pharmacological therapy or medical interventions are surveyed (Table 5). Additionally, laboratory investigations that are part of routine diagnostics (e.g. TSH, FT4, total T3, inflammation parameters, total protein etc.) are complemented by those parameters that are collected for the study (total T4, free T3 and antibodies against iodothyronines as well as thyroid tissue). As all required specimens are taken in the course of routine diagnostic procedures, additional assays, but no additional blood samples are necessary.

**Table 5 T5:** Schedule of evaluation points

	EP 1.0	EP 1.1	EP 1.2	EP 1.3	EP 1.999
	Screening	After 24 hours	After 72 hours	Weekly	After discharge

**Screening**					
Inclusion and Exclusion criteria	•	•			
Informed consent			°	°	°
**Demography**					
Age, Gender					•
History	•				
**Laboratory examinations**					
TSH, TT4, FT4, TT3, FT3		•	•	•	
rT3			•		
Total protein, Albumin		•	•	•	
BC, CRP, ATIII, Fibrinogen		•	•	•	
Thyroid antibodies, T4/T3-Abs.		•			
**Other investigations**		•	•	•	
Temperature, Horowitz-Quotient					
Vital signs	•	•	•	•	
**Evolution data**					
Medication	•	•	•	•	•
APACHE-II-/SAPS-II-Score, GCS		•	•	•	•
Diagnosis		•			•
HD/CVVH/CVVHDF	•	•	•	•	•
IABP	•	•	•	•	•
Persistent organ failure					•
Outcome (survival etc.)					•

	EP 2.0	EP 2.1	EP 2.2	EP 2.3	

	After transfer to peripheral ward	After 3 months	After 6 months	After 1 year	

**History and clinical data**					
Burch-Wartofsky score	°	°			
Medication	°	°	°	°	
Vital signs	°	°	°	°	
**Laboratory examinations**					
TSH, TT4, FT4, TT3, FT3	°	°			
**Neuropsychological data**					
Number connection test	°	°			
RWT	°	°			
SKT	°	°			
HADS	°				
SF36		°	°	°	
**Other investigations**					
Thyroid ultrasonography	°	°			
Outcome (survival etc.)	°	°	°	°	

•: Scheduled at indicated EP.

°: Scheduled after transfer to peripheral ward.

When patients have been transferred to a peripheral ward they are subjected to a single additional evaluation point (EP 2.0) surveying neuropsychological data covering anxiety, depression, speed of information processing and memory (see second part of Table 5). After discharge, they will be invited to repeated neuropsychological evaluations after 3, 6 and 12 months. This second part of the study is restricted to patients that gave informed consent (see below) and that have the mental and somatic ability to take part in this sub-study.

Patients that are admitted to an ICU a second time will only be observed up to that date, i.e. follow-up observation will stop after readmission to the ICU.

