### Statistics

The main null-hypothesis to be tested is that the decision-criteria presented in Table 2 lead to results that are independently distributed from the prognosis of included patients. Risk stratification will be performed with log rank test and Cox regression; end points are mortality, length of stay in hospital (LOSIH), length of stay in intensive care unit (LOSICU) and ability to work after discharge.

Cross sectional analysis will be done with the chi-squared test (for categorial data) and Student's t-test (for continuous data).

Multivariate regression analysis will be used to investigate correlation between quantitatively determined components of thyroid homeostasis and influencing pathophysiological factors.

Missing data analysis will be performed with "modern" procedures like EM algorithm and multiple imputation [25], if required.

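### Stopping all observation at ICU readmission conflicts with mortality and hospital stay as end points and is likely to censor informatively

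*Protocol article*

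**What the plan says.** The rule closes the section Follow-up and Evaluation Points, after Table 5: "Patients that are admitted to an ICU a second time will only be observed up to that date", restated as "follow-up observation will stop after readmission to the ICU". Neither half exempts vital status or the date of leaving hospital.

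Under Statistics, the main null hypothesis is that the Table 2 decision criteria "lead to results that are independently distributed from the prognosis of included patients". The method is fixed: "Risk stratification will be performed with log rank test and Cox regression". So are the outcomes: "end points are mortality, length of stay in hospital (LOSIH), length of stay in intensive care unit (LOSICU) and ability to work after discharge". No time horizon for mortality is given, and the article does not say whether LOSICU is the first ICU stay or all ICU days.

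Table 5 has an outcome row, beginning "Outcome (survival etc", in both parts. In the first part it is due once, at EP 1.999, after discharge. In the second part it is due at EP 2.0 to 2.3, that is, on the ward and at 3, 6 and 12 months. The later records exist for a subset only: "This second part of the study is restricted to patients that gave informed consent".

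The missing-data sentence offers "procedures like EM algorithm and multiple imputation" if needed and does not mention readmission.

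**The concern.** Log-rank and Cox analyses treat a censored patient as having the same later risk as comparable patients still under observation. Return to intensive care usually signals deterioration, so that assumption is doubtful at exactly the moment when this rule censors. An analysis plan cannot recover deaths or dates that were never collected. Standard EM or multiple imputation does not readily help either, because it relies on the observed data explaining why the rest are missing.

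At stake are the mortality figures, the hospital-stay end point and, through them, the estimates of how well each decision criterion predicts prognosis.

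**Working it through.** **Setting the sections side by side.** Read as written, the stopping rule cancels every outcome record in Table 5 that is still due when a patient is readmitted. For consenters this includes EP 2.1 to 2.3. For everyone it includes EP 1.999 if that point means hospital discharge. The Statistics section nevertheless needs those records for mortality and LOSIH. Nothing in the article says that vital status is still obtained, or that readmission is a competing or composite event.

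**Inputs.** The article gives no readmission rate, death rate or length of stay, so it has no figure on this point to reproduce. Only the planned 650 patients comes from it (Sample size and power calculation). The rest are assumptions:
- m = death in the index ICU stay, 15-25%
- r = readmission among ICU survivors, 3-10%
- q = death after readmission, 20-40%
- w = post-ICU death in survivors not readmitted, 5%

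**Deaths missed.**
- True mortality = m + (1 − m)[rq + (1 − r)w]
- Deaths missed per 650 = 650(1 − m)rq
- Share of all deaths = (1 − m)rq / true mortality

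Low end (m = 0.25, r = 0.03, q = 0.20):
- missed: 650 × 0.75 × 0.03 × 0.20 = 2.9
- true mortality: 0.25 + 0.75 × (0.006 + 0.0485) = 29.1%
- share: 0.0045/0.291 = 1.5%

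High end (m = 0.15, r = 0.10, q = 0.40):
- missed: 650 × 0.85 × 0.10 × 0.40 = 22.1
- true mortality: 0.15 + 0.85 × (0.040 + 0.045) = 22.2%
- share: 0.034/0.222 = 15%

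**Absolute mortality.**
- If readmitted patients are counted as alive, the shortfall is (1 − m)rq: 0.45 to 3.4 percentage points.
- If they are censored as though non-informatively, the estimate is m + (1 − m)w and the shortfall is (1 − m)r(q − w). This runs from 0.75 × 0.03 × 0.15 = 0.3 points to 0.85 × 0.10 × 0.35 = 3.0 points. Mortality is understated whenever q exceeds w.

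**Association between criterion and death.** Take m = 25% for criterion-positive and 15% for criterion-negative patients, q = 30% and w = 5%. Censoring at readmission gives 28.75% v 19.25%, a risk ratio (RR) of 1.49 and a risk difference of 9.5 points, whatever the readmission rates. The truth depends on them:

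| Readmission, positive v negative | True mortality | True RR | RR when censored | True difference |
|---|---|---|---|---|
| 10% v 5% | 30.6% v 20.3% | 1.51 | 1.49 | 10.3 points |
| 7% v 7% | 30.1% v 20.7% | 1.45 | 1.49 | 9.3 points |

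The first row is biased towards the null and the second away from it.

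A second set of assumptions (m = 20% v 10%, q = 30%, w = 4%), with readmitted patients counted as alive, shows the same reversal:
- Readmission 12% v 5%: true 25.7% v 14.8% (10.9 points, RR 1.74); recorded 22.8% v 13.4% (9.4 points, RR 1.70).
- Readmission 7% in both groups: true 24.7% v 15.2% (RR 1.62); recorded 23.0% v 13.3% (RR 1.72).

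**Length of stay.** If readmission falls within the same hospital stay and 7-21 days (assumed) remain, the mean LOSIH lost per ICU survivor is r × days: from 0.03 × 7 = 0.2 to 0.10 × 21 = 2.1 days. A readmission after hospital discharge leaves the index LOSIH complete. LOSICU loses nothing if it is the index stay, which has ended before any readmission.

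**The case against.** The rule follows directly on the description of the ward and 3-to-12-month assessments. It may be meant to end scheduled evaluations, or to prevent double enrolment and thyroid measurements confounded by a second critical illness, rather than to stop outcome recording. If EP 1.999 means ICU discharge, mortality in the index ICU stay is complete. The full protocol, not shown, may fix a mortality horizon. These are fair points about intent, but the wording is broad, and none of these purposes requires vital status or discharge date to go unrecorded.

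A reader might infer three stronger things that the article does not support.
- That LOSICU is biased: only if it is cumulative, which is not stated.
- That the criterion-prognosis association is pulled towards the null: this needs readmission to be sufficiently more frequent in criterion-positive patients, and equal readmission rates moved the RR the other way.
- That those lost are the sickest ICU survivors: plausible, but an inference.

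The size can also be made to look larger by leaving index-ICU deaths out of the denominator. On the main assumptions, rq/[rq + (1 − r)w] is 0.006/0.0545 = 11% to 0.040/0.085 = 47% of post-ICU deaths, against 1.5-15% of all deaths. Both are correct, but the second fits a mortality end point counted from inclusion in the study.

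**Conclusion.** The contradiction stands: as written, the stopping rule removes outcome data that the mortality and LOSIH end points and the Table 5 outcome rows require, and nothing elsewhere in the article repairs it. Censoring is likely to be informative, with absolute mortality understated by roughly 0.3 to 3.4 points, or 3 to 22 missed deaths per 650 patients, on the assumed rates. LOSIH is cut only for readmission within the same hospital stay. The direction of bias in the prognostic association is not determined, and in the examples the RR moved modestly, by 0.02 to 0.10. This should be fixed. It does not show that the main comparison is invalid, and its true size depends on readmission and death rates that the article does not report.

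**What to change.** Limit the rule to the scheduled laboratory and neuropsychological evaluation points and to re-enrolment. Then:
- keep recording vital status and hospital discharge date through readmission, to EP 1.999 for all patients and to EP 2.1-2.3 for consenters;
- record readmission as an event with its date, not as a reason for censoring, and state how it enters the survival analysis;
- state whether LOSICU is the index stay or cumulative ICU days;
- reconcile the rule with the outcome rows of Table 5;
- retrieve these fields from hospital records for readmitted patients among the 470 already included (Status of the study).

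The cost is an amended sentence and a small chart look-up, with no extra blood samples or visits. The first part runs without consent under an approved reduced protocol and identities sit in a separate list, so the look-back may need an ethics notification and controlled re-identification. Readmissions to other hospitals may remain incomplete, and their number should be reported.

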### Sample size and power calculation

The AQUA-FONTIS study has a planned sample size of 650 patients. On the premise of a beta level of 0.1 (corresponding to a power of 0.9), an alpha level of 0.05, and standard deviations and event rates as observed in the literature and in this study to date, between 200 and 566 patients would be required, depending on the objective in question.

With an appropriate safety-margin a total required number of 650 patients results. Most questions could be answered with 500 patients, however.

### Data management

Data are stored as electronic case report forms (eCRF) on a Macintosh server in a network-based relational database that has been developed with FileMaker Pro 5.5 (FileMaker, Inc., Santa Clara, CA, USA). It accommodates important principles of data protection by the fact that patient data are stored in pseudonymised form, i.e. they are referred to by number only, while mapping to patient names is only possible with an external list that is stored separately from the database. Additionally, the server is operating in the hospital's intranet with access from outside being blocked by a firewall. Data security is provided by a combination of established methods that cover regular backups and archiving as well as galvanic isolation of the server by an uninterruptible power supply. Operation of the server in a locked, dedicated room that is inaccessible for unauthorized persons serves both data protection and data security.

Other benefits of this database-founded approach are the ability to store very large amounts of information and the option to enter data from several wards simultaneously.

### Statistics

The main null-hypothesis to be tested is that the decision-criteria presented in Table 2 lead to results that are independently distributed from the prognosis of included patients. Risk stratification will be performed with log rank test and Cox regression; end points are mortality, length of stay in hospital (LOSIH), length of stay in intensive care unit (LOSICU) and ability to work after discharge.

Cross sectional analysis will be done with the chi-squared test (for categorial data) and Student's t-test (for continuous data).

Multivariate regression analysis will be used to investigate correlation between quantitatively determined components of thyroid homeostasis and influencing pathophysiological factors.

Missing data analysis will be performed with "modern" procedures like EM algorithm and multiple imputation [25], if required.

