### Objectives of the AQUA FONTIS project

The AQUA FONTIS study (**a**pproach to a **qua**ntitative **f**ollow-up **o**f **n**on-**t**hyroidal **i**llness **s**yndrome) is primarily intended to develop a clear-cut definition and classification of NTIS (Table 1). Overall, this project is proposed to deliver a prognostic aid by providing a differentiated classification, to contribute to a standardised, rational and inexpensive diagnostic procedure in form of quantitative indices, and to lay the foundation for future therapeutic trials by identifying subgroups that may benefit from therapy.

**Table 1 T1:** Proposed "HPD" classification

**Facet**	**Possible values**
Hypothalamic-pituitary dysfunction or adaptation ("H")	H0: Normal TSH secretion, adequate to T4 level H1: Thyrotropic insufficiency
	
Impaired plasma protein binding ("P")	P0: Normal binding to plasma proteins P1: Normal binding with reduced levels of plasma proteins P2: reduced binding to proteins within normal levels P3: reduced binding and reduced protein levels
	
Reduced deiodation ("D")	D0: Normal deiodation D1: Reduced deiodation activity

Example: H1P0D1: Thyrotropic insufficiency with reduced deiodation and normal protein binding.

Outcome measure of this primary objective is the comparison of different decision criteria as presented in Table 2. These criteria are assessed with regard to the prognosis of the patients. Additionally, the significance of an innovative physiological index approach (SPINA) [21] is to be evaluated regarding its applicability for differential diagnosis between NTIS and latent thyrotoxicosis. It will therefore be evaluated in terms of sensitivity, specificity and likelihood ratios with ROC analysis.

**Table 2 T2:** Decision criteria

**Criterion**	**Definition**
Thyrotropic insufficiency	a) Reduced levels of both TSH and free T4. b) Thyrotroph T4 Sensitivity Index (TTSI) reduced below its reference interval.
	
Reduced plasma protein binding	a) Reduced relative ratios of bound and free hormone levels b) Reduced apparent dissociation constant of T3 at thyroxin binding globulin (K_30_)
	
Reduced deiodation	a) Reduced level for free T3 b) diminished T3/T4-ratio c) reduced sum activity of peripheral 5'-Dejodinase (G_D_^)

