## Discussion

The **a**pproach to a **qua**ntitative **f**ollow-up **o**f **n**on-**t**hyroidal **i**llness **s**yndrome (AQUA-FONTIS study) has been designed to develop standardised diagnostic and classification criteria for NTIS. Apart from identification and differentiation of distinct functional states of thyrotropic feedback control in the context of critical illness, this study will help to assess the correlation of variables that quantify the components of NTIS with independent predictors of evolution, survival or pathophysiological condition. Additionally, it will evaluate the effect of influencing or disturbing factors like medication or interventional procedures.

In the past, many studies dealt with the impact of severe diseases on thyroid metabolism [1-8]. However, they had inconsistent results, which may be the result of lacking standardised criteria. The objective of the AQUA FONTIS project is to provide more clear-cut decision criteria for prognosis and possibly therapy of affected patients. These may help to make future studies comparable.

However, also the AQUA FONTIS study is faced with several limitations. These predominantly accrue from the fact that most patients receiving intensive care are not able to give informed consent [26,32]. We therefore had to constrain the possible investigations to methods that are purely observational or use patient sera that were obtained for routine diagnostics. Due to their extensive ethical and legal implications, we were e.g. not able to investigate genetic aspects of NTIS without informed consent: Although deferred consent for genetic investigations could be obtained from surviving patients this is by nature not possible in persons that are admitted as emergency cases and die early, so that a relevant bias would be to expect [27].

Additionally, the fact that a high proportion of patients will be admitted in cases of accidents or emergency makes it difficult to control relevant influencing factors. Conditions like existing thyroid diseases or previous medication may therefore in some cases be missed. Furthermore, stratification will be impossible.

These restrictions are shared by all observational studies. Alternative forms of data acquisition may seem more appropriate from a pure statistical point of view. However, the mentioned medical and ethical marginal conditions render them impossible.

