Its two-module structure, covering an observational part before patients gave consent and a more comprehensive sub-study that is traversed after consent was obtained, helps to overcome some of the limitations of the AQUA FONTS study. Additionally, the number of patients that could already be included up to now gives reason to believe that some of the poorly controllable influencing factors may partly be compensated by a large final case number. We are therefore convinced that this study will help to identify decision-parameters for defining states of particular importance with respect to the prognosis of affected patients. These may lay the basis for future epidemiological or therapeutic trials.

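### The primary outcome measure is a comparison of rival Table 2 criteria, but the main null hypothesis tests only whether the criteria are associated with prognosis

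*Protocol article*

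**What the plan says.** The section on the objectives of the project fixes the primary outcome measure: "Outcome measure of this primary objective is the comparison of different decision criteria as presented in Table 2". The yardstick follows in the next sentence: "These criteria are assessed with regard to the prognosis of the patients". Table 2 lists rivals under three facets: two definitions of thyrotropic insufficiency, two of reduced protein binding and three of reduced deiodation.

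The Statistics section sets the main hypothesis: "The main null-hypothesis to be tested is that the decision-criteria presented in Table 2 lead to results that are independently distributed from the prognosis". For prognosis it adds "Risk stratification will be performed with log rank test and Cox regression", with four end points (mortality, hospital stay, ICU stay, ability to work). It also says "Cross sectional analysis will be done with the chi-squared test (for categorial data) and Student's t-test (for continuous data". The multivariate regression there relates thyroid components to pathophysiological factors; prognosis is not its outcome.

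ROC methods appear once, for the SPINA index in separating NTIS from latent thyrotoxicosis: "It will therefore be evaluated in terms of sensitivity, specificity and likelihood ratios with ROC analysis".

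Among its limitations the Discussion says that influencing factors are hard to control in emergency admissions, so that thyroid disease or earlier medication may be missed. It continues "Furthermore, stratification will be impossible", and later hopes that "some of the poorly controllable influencing factors may partly be compensated by a large final case number".

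**The concern.** The primary question is which of several competing definitions of the same component serves best for prognosis. The main null asks something else: whether the criteria relate to prognosis at all. If all seven were associated with death, the null would be rejected and the choice between definitions would be no nearer. The Background already accepts that NTIS goes with a worse prognosis, so rejection is largely expected and tells the reader little.

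The gap invites a familiar mistake, which is to read one small p-value beside one large one as evidence that the first criterion is better. A classification meant to guide later therapeutic trials could then rest on chance differences between correlated criteria.

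Two lesser points belong with this. A prognostic aid is most useful if it adds to the severity scores already in use, and the main null does not address that. The Discussion also offers a large case number as partial compensation for uncontrolled factors. A larger sample reduces random error but not confounding.

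**Working it through.** **1. The two statements side by side.** With 2, 2 and 3 criteria in the three facets of Table 2, the within-facet comparisons number 1 + 1 + 3 = 5. The main null, read jointly or criterion by criterion, contains none of them. Log rank, chi-squared and t-tests each set one criterion against an outcome. A Cox model could hold several criteria, but no contrast is named. ROC analysis is assigned to a different question.

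**2. The plan's own sample size.** The article gives alpha 0.05, power 0.90, a range of 200 to 566 and a planned total of 650. It gives no effect size, standard deviation or event rate, so the range cannot be reproduced. For scale only, with two equal groups and a two-sided test, n per group = 2(1.960 + 1.282)²/d²:
- d = 0.46 gives 100 per group, total 200.
- d = 0.2725 gives 284 per group, total 568.
- Proportions of 0.15 and 0.26 give a total of 562.

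These are sizes for a simple two-group difference. Nothing shown ties the range to a difference between two criteria measured in the same patients. The margin is 650/566 = 1.148.

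**3. Separate tests do not make a comparison (assumed inputs).** Take two equally prognostic criteria whose test statistics correlate 0.5. The chance that exactly one is significant is 2 × (power − P(both significant)), from a bivariate normal:
- power 0.90: 2 × (0.900 − 0.832) = 13.5%
- power 0.70: 2 × (0.700 − 0.557) = 28.6%
- power 0.50: 2 × (0.500 − 0.333) = 33.3%

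The opposite failure was simulated at N=650: two continuous indices correlated 0.5, intercept −1.3 on the logit scale, 300 runs per setting. The direct comparison was a paired DeLong test of the two AUCs.

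| Log-odds per SD (criterion 1 / 2) | Both separate t-tests reject | Direct comparison rejects |
|---|---|---|
| 0.4 / 0.4 | 100% | 4% |
| 0.5 / 0.3 | 100% | 15% |
| 0.6 / 0.2 | 100% | 48% |

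The separate tests look the same in all three rows.

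**4. Case number and confounding (assumed inputs).** A criterion with 50% prevalence has no effect on death once severity is known. Severity has an odds ratio of 2.0 or 2.5 per SD and correlates 0.2 to 0.5 with the underlying index; 400 runs per cell. Rejection by the unadjusted chi-squared test:

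| Correlation / odds ratio | N=200 | N=566 | N=650 |
|---|---|---|---|
| 0.2 / 2.0 | 10% | 18% | 21% |
| 0.2 / 2.5 | 10% | 25% | 31% |
| 0.3 / 2.0 | 15% | 38% | 40% |
| 0.3 / 2.5 | 18% | 50% | 53% |
| 0.5 / 2.0 | 33% | 75% | 78% |
| 0.5 / 2.5 | 55% | 91% | 94% |

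The severity-adjusted test stays at about 3% to 7% throughout. More patients make the crude association more certain; they do not remove its source.

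**The case against.** Several stronger readings are tempting, and the document does not support them.

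A reader might infer that no adjusted analysis is planned. The Statistics section names Cox regression, and its covariates are the kind of detail left to a full protocol or analysis plan that is not shown. Silence in a journal article does not establish that severity will be ignored.

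A reader might infer that the article counts on sample size to deal with severity. It does not. The factors it calls hard to control are mainly missed thyroid disease and earlier medication, and the wording is hedged. SAPS II and APACHE II are scheduled from the 24-hour evaluation onward. Only the general point stands, that case number improves precision and does not correct confounding.

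A reader might call the crude rejections in step 4 false positives. Under the null as written they are correct rejections, because a criterion linked to death through severity is still prognostic. They become errors only if the question is added value over severity, which the article does not state as its main hypothesis.

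Finally, no section says that criteria will be ranked by significance. The discordance figures show what would follow from that practice, not what is planned. The cases at 70% and 50% power also lie below the planned 90%.

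None of this closes the main gap. An adjusted Cox model for each criterion would still not compare one criterion with another.

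**Conclusion.** The point holds as a mismatch between two statements fixed in the article: a primary outcome measure that is a comparison, and a main null that contains none. Followed as written, the main test would not answer the primary question. This conclusion needs no assumed figure.

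The size of the consequence can only be illustrated. The 4% to 48% rejection by a direct comparison at N=650, and the crude rejection of 21% to 94% against 3% to 7% when adjusted, rest on assumed correlations, effects and mortality. The paired simulation used continuous scores; the Table 2 criteria are yes/no decisions, which would usually be harder to tell apart. The article's range of 200 to 566 is not shown to cover the paired contrast, so the study should not be presented as powered for it.

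**What to change.** In the Statistics section, keep the tests of association and add the analysis that matches the primary outcome measure:

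- For each facet, compare the rival criteria directly in the same patients by the paired difference in C-index for mortality, with bootstrap confidence intervals and optimism correction.
- Report each criterion's added value in a Cox model that includes age and the APACHE II or SAPS II score from EP 1.1.
- State that the sample-size range of 200 to 566 is not shown to cover these contrasts, and report them as estimates with intervals.
- In the Discussion, limit the remark on case number to precision.
- Label any illustration of confounding as assumption-based and give its range.

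The severity scores and age are in Table 5, so the cost is analysis and wording, with no new data collection. The paired contrasts will have wider intervals than the single-criterion tests and may leave some rivals unseparated. Adjusted effects will be smaller than crude ones.
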